## Abstract

**Introduction:**

We aim to determine the effectiveness of a school-based violence prevention programme implemented in Jamaican preschools, on reducing the levels of aggression among children at school, and violence against children by teachers.

**Methods and analysis:**

This is a 2-arm, single-blind, cluster-randomised controlled trial with parallel assignment. Clusters are 76 preschools in Kingston, and all teachers and classrooms in the selected schools are included in the study. In addition, a random sample of up to 12 children in the 4-year-old classes have been selected for evaluation of child-level outcomes. The intervention involves training teachers in classroom behaviour management and in strategies to promote children's social-emotional competence. Training is delivered through five full-day workshops, monthly in-class coaching over 2 school terms, and weekly text messages. The primary outcome measures are: (1) observed levels of child aggression and (2) observed violence against children by teachers. Secondary outcomes include observations of the levels of children's prosocial behaviour and the quality of the classroom environment, teachers’ reports of their mental health, teacher-reported child mental health, direct tests of children's self-regulation and child attendance.

**Ethics and dissemination:**

If this intervention were effective at improving the caregiving environment of young children in school, this would have significant implications for the prevention of child mental health problems, and prevention of violence against children in low and middle-income countries where services are often limited. The intervention is integrated into the school system and involves training existing staff, and thus, represents an appropriate strategy for large-scale implementation and benefits at the population level. Ethical consent for the study was given by the School of Psychology Ethics and Research Committee, Bangor University (ref: 2014-14167), and by the University of the West Indies Ethics Committee (ref: ECP 50,14/15).

**Trial registration number:**

ISRCTN11968472; Pre-results.

## Introduction

Violence is a leading worldwide public health problem, and makes a substantial contribution to the burden of disease at the global level.^1^ Interventions in early childhood are an important component in the primary prevention of violence. Training young children's caregivers in behavioural strategies to reduce child aggression and promote child social skills can (1) prevent the early development of antisocial behaviour and (2) reduce violence against children by caregivers.

Children with social, emotional and behavioural problems at school entry are at risk for many negative outcomes throughout life including juvenile delinquency, academic underachievement and crime and violence in adulthood.^2^ Schools offer a logical public health setting for implementing preventative interventions, and reviews of school-based violence prevention programmes in high-income countries indicate significant reductions to children's aggressive behaviour and increases in child competencies,^3^ with some evidence that benefits are sustained into the late teenage and adult years.^4^ However, there is limited evidence of the effectiveness of school-based preventative interventions in low and middle-income countries (LMIC) where schools often have poor physical conditions, high child-staff ratios, few classroom resources and low levels of teacher training.

School-based violence prevention programmes can also reduce the use of violence against children by teachers.^5^ This is important for many LMIC where corporal punishment is a commonly used behaviour management strategy; though the evidence for effective teacher training interventions in LMIC is limited.^6^ A recent study demonstrated a reduction in physical violence by school staff against primary school children in Uganda.^7^ Exposure to corporal punishment in schools is associated with poor child mental health, poor social skills, increased aggression, low levels of school achievement and increased school drop-outs.^6^

Child mental health services are severely limited in LMIC,^8^ and there is a growing interest in integrating these services into educational settings. If treatment services are made available in schools, it will be important that the schools are also engaged in the primary prevention of child mental health problems and are providing a supportive environment for child mental health promotion.

### The Jamaican context

Violence prevention is a national and regional priority for Jamaica and the wider Caribbean.^9^ A survey of a small, but nationally representative sample of Jamaican 5–6-year-old children reported a prevalence of externalising disorders of 12%, and none of these children had received any form of medical or social services.^10^ The prevalence is likely to be substantially higher in low-income, inner-city areas.^11^ In an efficacy trial, we screened 1733 children from 24 preschools in disadvantaged areas of Kingston using teacher reports, and 21% had four or more symptoms of conduct problems.^12^

Corporal punishment is also widespread in Jamaica and although banned by law in early childhood institutions, it continues to be widely used.^5^ Corporal punishment by teachers is associated with poor school achievement among Jamaican primary school children.^13^ In focus groups, although parents and teachers of preschool children reported using corporal punishment to manage child behaviour, they also reported that it is undesirable and ineffective.^14^ Jamaica is an ideal location for integrating a violence prevention programme into preschools due to the well-established preschool network, with over 97% of 3–5-year-old children enrolled in school.

### Development of the Irie Classroom Toolbox

The intervention to be used in this study has been developed from our experiences implementing and evaluating behavioural interventions to prevent violence and promote child mental health in Jamaican preschools. Our first step was to conduct formative research followed by a pilot study in five preschools in which we trained teachers in classroom behaviour management, and the research team delivered a 14-session curriculum unit on social and emotional skills in each intervention classroom. Teachers were trained through seven full-day workshops, and were provided with extensive in-class support (1 h/week for 6 months) and a monthly, individual consultation session. The intervention was based on the Incredible Years Teacher Training Programme,^15^—an evidence-based programme to prevent and treat child conduct problems, although we made some modifications to facilitate use with teachers with limited prior training. A qualitative and quantitative evaluation of this pilot study was conducted, and we found large benefits to teacher practices and classroom atmosphere (mean effect size (ES)=2.15),^5^ and significant benefits to teacher-reported child mental health (mean ES=0.38).^16^ The qualitative evaluation highlighted the aspects of the intervention teachers found most useful, and why, what strategies were misunderstood, and teachers also provided suggestions for improving the intervention.^17^ The results of the pilot study were used to prepare additional training materials to make it more suitable for the Jamaican preschool context. These training materials included producing Jamaican video vignettes, developing hands-on activities, role-plays and group work to introduce key principles of behaviour management, and adding training content to address teachers’ unmet needs. We also developed a curriculum to teach social-emotional skills that could be integrated into ongoing teaching and learning activities, rather than using a separate curriculum unit.

We implemented and evaluated this modified intervention in an efficacy trial in 24 preschools.^12^ Teachers attended eight full-day workshops and received 1 hour of in-class support each month over 4 months. A quantitative and qualitative evaluation was again conducted, and benefits to teacher practices and classroom atmosphere were of a similar magnitude to those found in the pilot study (mean ES=2.5), despite the large reduction in in-class support. The intervention also produced meaningful benefits to high-risk children's conduct problems and prosocial behaviour at home and at school with a mean ES of 0.49 SD.^12^ The qualitative evaluation focused on what aspects of the training were most useful and least useful, and factors affecting teachers’ implementation of the strategies.

We have developed ‘The Irie Classroom Toolbox using the results of the efficacy trial and our ongoing documentation of training Jamaican preschool teachers. Observational data of teachers’ use of strategies combined with teachers’ and facilitators’ reports and ratings of strategies which are easy to use, most effective and most relevant have been used to identify the key evidence-based behaviour principles that are most suitable and effective. In addition, teachers’ and facilitators’ reports of preferred training methods have been used to develop the training materials and to develop a protocol for the provision of in-class support. The modified intervention is based on the concept of a ‘toolbox’ consisting of ‘evidence-based kernels and behavioural vaccines’,^18^ that are used across a range of evidence-based child behaviour modification interventions, and uses evidence-based behaviour change techniques in the training process.^19^ This low-cost training package is designed to be suitable for use with teachers with limited training and working in poorly resourced settings in LMIC, and aims to facilitate widespread adoption of key child behaviour management strategies.

### Aims

The aims of this trial are to evaluate the effect of a universal violence prevention programme implemented in inner-city preschools in Kingston, Jamaica. The intervention involves training teachers in classroom behaviour management and in strategies to promote child social-emotional competence. The primary aims of the study are to reduce teachers’ use of violence against children and to reduce aggression among children. Additional aims are to improve the quality of the classroom environment, promote child social skills, self-regulation, mental health and school attendance, and to promote teachers’ mental health. The cost-effectiveness of the intervention will also be evaluated.

## Methods and analysis

### Design

The trial is a 2-arm, single-blind, cluster-randomised trial with parallel assignment. Clusters are community preschools catering to children aged 3–6 years in Kingston, Jamaica. Inclusion criteria are that preschools are situated in urban areas of Kingston, have 2–4 classrooms, and an average of at least 10 children per class. A random sample of 76 preschools were selected from all eligible schools. All teachers in the selected preschools are participating in the study, and a random sample of children in the 4-year-old class of each preschool was selected to participate in the evaluation. Children were eligible to participate in the evaluation aspect of the study if their average attendance in the preceding two terms was greater than 50%, and they have no obvious disability. However, all children within the school receive the intervention.

### Intervention

#### Content of training

The intervention involves training preschool teachers using ‘The Irie Classroom Toolbox’. The toolbox consists of four modules: (1) creating an emotionally supportive classroom environment, (2) preventing and managing child behaviour problems, (3) teaching social and emotional skills to children, (4) individual and class-wide behaviour planning. The first two modules consist of training in a number of discreet strategies which are feasible, relevant and flexible, and have readily observable effects (eg, verbal praise, use of visual cues). Each behaviour kernel can be used alone or in conjunction with others to modify child behaviour. This is a pragmatic approach that allows teachers to choose which strategies to use and how to implement them depending on their own teaching style, their classroom context and the needs of the children in their class. The third module provides teachers with lesson plans, visual aids and classroom activities to integrate the teaching of social-emotional competence into ongoing teaching and learning activities.

#### Process used in training

The training process used to deliver the content is based on evidence-based behaviour change techniques^19^ (eg, goal setting, collaborative problem-solving, positive feedback, role playing), and this process maximises the likelihood that teachers will be able to understand and apply the strategies. The intervention is solution-focused which ensures the challenges associated with implementation of the strategies are recognised and overcome.

#### Intervention materials

The intervention materials for teachers include two booklets, three sets of picture cards and 14 sets of story cards. The booklets are (1) a ‘toolbox’ book giving simple, clear guidance on how and why to use each strategy and (2) an activity book of songs, games and lesson plans. The three sets of picture cards include pictures illustrating classroom rules, friendship behaviours and emotion faces designed to facilitate the teaching of key concepts to children. Fourteen stories are depicted in story cards, and they include a range of common classroom scenarios and strategies that children can use to overcome common problems (eg, the need to share materials, wait for a turn, etc). Each set of story cards includes a discussion guide for the teacher. There are two booklets for facilitators: (1) a training manual for conducting training workshops and (2) a coaching manual for in-class support sessions.

#### Intervention delivery

The intervention is being delivered to schools randomised to intervention in the 2015/2016 academic year. Four intervention facilitators are delivering the intervention through five full-day workshops, monthly in-class coaching and fortnightly text messaging. The in-class support is delivered during one teaching session (approximately 1 h) per month in each intervention classroom and involves coaching the teacher in selected strategies, performance feedback and collaborative problem-solving. The in-class support is designed to (1) increase teachers’ confidence and motivation in using the strategies, (2) help teachers to problem-solve and (3) help tailor the strategies to the individual's classroom context. The fortnightly text messages are used to remind and encourage teachers. Each class is provided with a small amount of educational materials (eg, building blocks, books) to facilitate their use of the strategies taught.

#### Control condition

Teachers in control schools receive the same educational materials at the same time as intervention schools, and they attend the regular teacher training days provided by the Ministry of Education and Early Childhood Commission. They do not receive the Irie Classroom Toolbox training workshops, in-class support, text messages and intervention materials. Control teachers will be trained in the intervention in the 2017/2018 academic year.

### Outcome measures

All measures are collected at baseline (in the summer term of 2015) and will be repeated at post-test (summer term of 2016). All classroom and teacher-level outcomes will also be collected at 1-year follow-up (summer term of 2017). Classroom and teacher-level outcomes will be collected in the control schools only in the summer term of 2018.

All data are collected by research assistants using pencil and paper methods. Data collectors will be trained over a minimum of a 4-week period before each round of measurements. Inter-rater reliabilities will be assessed for all measures, and values of over r>0.8 will be required. Training will continue until this standard is attained. Ongoing inter-rater reliabilities will be conducted on a minimum of 5% of all measurements. Observers and testers will be rotated across classrooms and schools to ensure any variance among data collectors is not systematic. Data will be monitored weekly for such systematic variation and to ensure inter-rater reliabilities >0.8 are maintained. All questionnaire and test data will be checked by the trial manager on a daily basis for missing or erroneous data, and data will be checked weekly by a content expert to monitor compliance with the data collection protocols.

#### Primary outcomes

We have two primary outcome measures to allow us to evaluate the effect of the intervention on violence prevention at the level of (1) the teacher and (2) the children. Both measures involve observations by independent observers blind to the study design, hypothesis and group status.

Observations of teachers’ use of violence against children. These take place over two school days. Observations are continuous over one school day and for five 20 min intervals spread over the second school day linked to the schedule for class-wide observations (see below). Event recording will be used to record each use of corporal punishment, verbal abuse, and other abuse (eg, intimidation) by teachers. These behaviours are defined in an observation manual based on definitions used in Jamaican preschool classrooms previously.^5^ Teachers’ use of violence will be coded as a binary variable for analysis, with teachers coded as 1 if they use violence versus 0 if they do not. If the percentage of teachers using violence is more prevalent than anticipated and/or has wide variability in scores, then the variable will be coded as a count using three to four categories to represent the spread of the data.

Observations of class-wide child aggression. These take place over five 20 min intervals spread over one school day, and is based on a rating scale used previously in Jamaican preschool classrooms.^5^ At the end of each 20 min interval, observers rate the overall level of children's aggression in the classroom on a seven-point rating scale. The mean score over the five observations will be used in the analysis. Ratings of classroom aggression during the early childhood years predict growth in child aggression over time.^20^

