### Sample size

The trial has two primary outcomes: level of class-wide aggression and violence against children. Using Tukey's method of correction for multiple testing,^33^ we require a significance level of 0.036 in each individual test to keep a Family-Wise Error Rate of 0.05.

Level of class-wide aggression. In a parallel group design, 72 classes in each group are sufficient to detect an ES of 0.5 SD, with 81% power at 0.05 level of significance. With a cluster size of three (3 classrooms/school), and assuming an intraclass correlation (ICC) of 0.25, the design effect is 1.5 (design effect=1+(cluster size–1)×ICC)) giving a required sample size of 108 classrooms per group, which yields 36 schools per group. We will recruit 38 schools (114 classrooms) per group (76 schools in total) to allow for 9% teacher loss.

Violence against children by teachers. In a parallel group design, 90 classes in each group are sufficient to detect a reduction from 60% to 35% with 87% power at 0.05 level of significance. With a cluster size of three (3 classrooms/school) and an ICC of 0.1 (based on data from our efficacy trial), the design effect is 1.2, giving a required sample size of 108 classrooms per group, which yields 36 schools in each group. As mentioned above, we will recruit two additional schools per group.

The analyses of the secondary outcomes is considered exploratory, and the significance level of the tests will not be adjusted for comparisons of multiple outcome.

Classroom and teacher-level measures. Similar to the primary outcome of level of classwide aggressions, we have 85% power at a 0.05 level of significance to detect a difference of 0.5 SD on the quality of the classroom environment and on teacher depression, self-efficacy and burn-out.

Child-level measures. In a parallel group design, 252 children in each group are required to detect a difference of 0.25 SD with 80% power at 0.05 level of significance. With 11 children per school, and an estimated intracluster correlation coefficient of 0.05, the design effect is 1.50 giving a required sample size of 378 children and 36 schools in each group. Our proposed sample includes 38 schools/group. We recruited children from the 4-year-old class: in classes with 12 or fewer children, all children were recruited; where there were more than 12 children, a random sample of 12 children were selected. The maximum sample size was 456 children/group.

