#### Statistical methods

The effect of intervention will be examined on an intention-to-treat basis, using multilevel multiple regression models for continuous outcomes and random effects logistical regression models for binary outcomes (and random effect for count outcomes such as Poisson or Negative Binomial if required), to take into account the hierarchical structure of the study. Tester/observer and intervention status (and child age and sex for child-level data) will be entered as fixed effects, and school (and classroom) entered as random effects.

Few studies have reported on mediators of intervention effectiveness in school-based preventative trials. We will explore whether change in teacher depression, self-efficacy and burn-out mediate the effect of intervention on teachers’ use of violence and levels of classroom aggression using standard techniques for multilevel mediation analyses. We will also examine whether teachers’ use of violence and the quality of the classroom environment mediate the effect of intervention on child mental health, self-regulation and attendance. Potential moderators of intervention effectiveness will also be investigated. We will examine whether teachers who use high levels of violence against children at baseline, and whether classrooms characterised by high levels of child aggression at baseline, benefit most from the intervention. We will also examine whether the child's sex moderates the effect of intervention on child mental health, social skills, self-regulation and school attendance.

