### Trial status

The study began in January 2015. Baseline data collection was conducted from May to June 2015. Intervention began in September and is currently underway.

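### The rule for coding the violence primary outcome depends on its own distribution, with no threshold for spread, no named data round and no requirement of blindness to arm; the pre-randomisation baseline data could fix it

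*Protocol article*

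**What the plan says.** **Default coding** (Primary outcomes). The outcome starts as binary: a teacher scores 1 for any recorded violence and 0 for none.

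**Switch** (same section). The default is replaced under a condition: "If the percentage of teachers using violence is more prevalent than anticipated and/or has wide variability in scores". In that case "then the variable will be coded as a count using three to four categories to represent the spread of the data". Either limb is enough. The prevalence limb has an implied anchor, the 60% assumed without intervention under Sample size. The variability limb has none. The choice between three and four categories and the position of the cut-points are left to the data.

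**Model** (Statistical methods). Random-effects logistic regression is planned for binary outcomes, with "random effect for count outcomes such as Poisson or Negative Binomial if required". The model is not tied to a particular coding.

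**Error rate and power** (Sample size). There are two primary outcomes, and "we require a significance level of 0.036 in each individual test to keep a Family-Wise Error Rate of 0.05". Violence is powered for the binary coding only: 60% to 35%, 90 classes per group before a design effect of 1.2, 87% power.

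**Baseline.** Outcome measures says that all measures were taken in the summer term of 2015 and are repeated in 2016. Allocation says that all baseline measurement preceded randomisation. Trial status says: "Baseline data collection was conducted from May to June 2015". The coding was therefore still conditional in the article after the baseline round had closed.

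**The concern.** The multiplicity allowance pays for one violence test. The rule lets the form of that outcome follow its observed distribution, and nothing in the article keeps the decision away from the arm comparison. If someone could see how the arms differ under ever/never, three-category and four-category codings before settling on one, the test would no longer run at 0.036. A positive finding on a primary outcome could then be put down to the coding.

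A switch also changes the effect being estimated, from a prevalence to a shift across categories, and leaves the basis on which power was calculated. That holds even for a blind choice, though a blind choice costs no type I error.

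**Working it through.** **1. The plan's own figures.**
- Per-test level by Tukey's correction for two outcomes: 1 - (1 - 0.05)^(1/√2) = 0.0356, which rounds to the stated 0.036.
- Power for 60% against 35% with 90 per group, two-sided (sidedness assumed). At 0.036 it is 87.4% with continuity correction and 87.0% by Fisher's exact test, matching the stated 87%. At 0.05 the same calculations give 90.1% and 89.4%. The stated power therefore goes with 0.036, although 0.05 is printed beside it.
- Design effect: 1 + (3 - 1) × 0.1 = 1.2, and 90 × 1.2 = 108 classes = 36 schools per group.

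**2. The fallback has a real purpose.** The planned odds ratio is (0.60/0.40)/(0.35/0.65) = 2.79. Hold it, with 90 per group at 0.036 and no continuity correction:
- control prevalence 60% (against 35%): power 90%
- control prevalence 80% (against 58.9%): power 84%
- control prevalence 90% (against 76.4%): power 64%

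**3. Type I error if the coding is chosen with arm visible.** From the article: 38 schools per arm, 3 classes per school, level 0.036. Assumed, because the article gives no count distribution: negative binomial counts with dispersion 0.7 or 1.5, a school effect with SD 0.6 on the log mean, and 60%, 80% or 90% of teachers using any violence. The resulting ICC of the binary coding was 0.02 to 0.09. There were 20,000 data sets per scenario with no effect, and each coding was tested by a t test on school means.

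The codings, added in order, were: ever/never; three categories (none, then split at the median of the positive counts); four categories (none, then split at their tertiles); a second three-category coding (0-1, then split at the upper tertile); log(1 + count). The table gives the proportion of data sets in which the smallest p value is below 0.036.

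| Any violence | Dispersion | Best of 2 | Best of 3 | Best of 4 | Best of 5 | Pooled rule |
|---|---|---|---|---|---|---|
| 60% | 0.7 | 0.0489 | 0.0563 | 0.0669 | 0.0688 | 0.0347 |
| 60% | 1.5 | 0.0532 | 0.0621 | 0.0745 | 0.0761 | 0.0370 |
| 80% | 0.7 | 0.0561 | 0.0673 | 0.0767 | 0.0809 | 0.0351 |
| 80% | 1.5 | 0.0568 | 0.0682 | 0.0790 | 0.0815 | 0.0372 |
| 90% | 0.7 | 0.0634 | 0.0756 | 0.0845 | 0.0885 | 0.0358 |
| 90% | 1.5 | 0.0602 | 0.0738 | 0.0844 | 0.0878 | 0.0369 |

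Any single coding fixed in advance rejected in 0.032 to 0.039 of data sets.

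**4. A choice that ignores arm.** The last column uses four categories if prevalence pooled over arms exceeds the scenario value, and ever/never otherwise. It stays at 0.035-0.037. The reason is general: with no effect, arm labels are exchangeable given the pooled data, so a rule that never looks at the labels does not favour either arm. Baseline data taken before randomisation have the same property.

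**5. Cross-checks.** For independent codings the rate would be 1 - (1 - 0.036)^k, which is 0.071, 0.104 and 0.136 for k = 2, 3 and 4. The simulated values lie below these, as expected for correlated codings. A second simulation used other assumptions (61% or 82% using violence, school SD 0.35). It gave 3.5-3.8% for one fixed coding, 5.5-5.9% for the better of two, 6.4-6.8% for the best of three and 7.3-8.3% for the best of five.

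**The case against.** The strongest defence is that the article describes one test with an if/then coding. Both triggers describe the distribution of the scores, not the difference between arms, and nothing permits running several codings and reporting the best. The only stated expectation before intervention is 60%. A comparison with that fits untreated data, such as baseline, at least as well as post-test data in which one arm is meant to fall to 35%. Cut-points, timing and blinding of the decision are commonly left to an analysis plan, which is not shown here.

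Most of this stands. A reader might infer that the coding will be picked from post-test results, or that the error rate already exceeds 0.036. The documents support neither. No data round is named, so the post-test reading is an inference, drawn only from the choice remaining open after baseline was complete. Even a choice on post-test data does no harm to the error rate if it is made on pooled data.

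Two limits on the figures also stand. At 80% or 90% prevalence the prevalence limb, followed literally, would remove ever/never, so choosing between it and a category coding would not be open. The test used was a school-level t test, not the planned random-effects model with observer as a fixed effect.

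The defence does not remove the point, because the article does more than leave a detail open. It states a switch for a primary outcome, and its variability limb can be judged only by eye. The Blinding section says that researchers are masked at post-test, but the measures it describes concern observers and interviewers, not whoever chooses the coding.

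**Conclusion.** The point holds in a conditional form. The coding of a primary outcome may change with the prevalence and spread of its own scores, under a rule that has no threshold for spread, no named data round and no requirement of blindness to arm.

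If the choice were made on post-test data with arm differences visible, the type I error could rise from 0.036 to roughly 0.05-0.06 for two codings, and to about 0.09 in the worst case examined. The worst case takes the smallest p value over five analyses, with illustrative cut-points. These sizes depend on assumed count distributions. If the choice is made on baseline data or on data pooled over arms, the error stays at about 0.036.

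This should be changed because the remedy is cheap and the necessary data are already held. It is not evidence that the planned test is invalid.

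**What to change.** Apply the switching rule once, to the violence data collected at baseline. Record in a dated amendment, before any post-test data are seen, the coding, the cut-points if categories are used, and the model that goes with them. Use the same coding at post-test and at the 1-year follow-up. Report any other coding as a sensitivity analysis.

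If baseline cut-points would leave sparse categories at post-test, for example because violence falls as hoped, an acceptable alternative is a single choice on post-test data pooled over arms, documented before unblinding.

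The cost is one tabulation of existing data and one paragraph. The downside is small: cut-points set on baseline may fit the post-test spread less well.
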